### Sample size

We planned to recruit a total of 102 HSAs. Our sample size estimation is based on change in proportions of the primary outcomes expected pre and post intervention. Assuming an alpha of 0.05, 97 HSAs would provide 80% power for a minimum detectable rate of change between 6 and 7% in referral, re-consultation and hospitalizations (one-sided test). We assumed a 1% urgent referral rate, based on the proportion of children identified as needing to be urgently referred at clinics in a previous study conducted in Malawi [11]. As an urgent referral rate of 8% has been estimated as a reasonable consensus referral rate at clinics in sub-Saharan Africa [43, 44] that are correctly adhering to IMCI, we assumed the addition of the SL eCCM App could improve urgent referral rates close to this estimate; a 6–7% change between the control and intervention was, therefore, a conservative estimate of this assumption. Given the short trial duration and potential of perceived elevated status through smartphone ownership in this setting [45], we did not expect many HSAs to drop out. We believed that recruiting 102 HSAs would be sufficient to accommodate potential dropout, to ensure we achieved our desired sample size. Power calculations were computed using the “Power and Sample Size” option in Stata v. 13 (StataCorp, College Station, TX, USA) [46] which is appropriate for rates, specifically “*longitudinal studies, where the same cases serve as their own controls over time*” [47].

A total of 300 parents/caregivers whose children were referred to a higher-level facility or re-consulted at a village clinic completed the PCQ. It was estimated that approximately 600 children would be eligible for referral to a health care facility assuming: a 1% referral rate among 4000 children in the control group (*n* = 40), a 7–8% referral rate (change 6–7% from the initial 1% referral rate) among the same number of children in the intervention group (*n* = 300) and a 6–7% under-referral rate in the control group (*n* = 260). Considering the challenges in identifying those who were referred but did not present at a health care facility, or those who were not referred but did visit a health care facility or represented at a village clinic, and the possible withdrawal or loss to follow-up of parents/caregivers, it is estimated that at least half (*n* = 300) of the eligible cases will be followed up as part of the cost evaluation.

We also interviewed 15 HSAs and 25 caregivers to explore barriers and facilitators to caregiver compliance with referral recommendations, as well as HSA and caregiver acceptability of the SL eCCM App. Pre-determining the number of participants needed in qualitative research is challenging since the underlying goal of achieving saturation is influenced by factors including interview type (typically one-to-one interviews foster deeper but more narrow exploration of concepts than focus groups, due to absence of exchange of opinions which broaden scope), homogeneity of interviewees, and skill of the researcher (among other things). Guest et al. indicated 12 semi-structured interviews as sufficient to attain saturation [48]. Since our approach is exploratory rather than theoretical, we believed that our target sample size would be sufficient to address our research question and accommodate any heterogeneity among either participant population.

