Utilizing mobile health (mHealth) technologies (e.g., smartphones, tablets) to deliver CCM could encourage the dispensation of more appropriate treatment recommendations [25] thereby increasing urgent referral rates. Potential improvements may be underpinned by a combination of better control of how the end-user navigates through assessment questions (e.g., built-in validation rules forcing completion of relevant fields with valid data before advancing to the next field/screen) [26]; enhanced CHW motivation linked to the prestige of using advanced technology in a predominantly paper-based health care system; automated presentation of the next-steps reducing reliance on memory [27], and heightened perceived efficacy and caregiver trust in CHWs’ decisions linked to clearer explanations about the child’s condition and recommended treatment [27].

Despite the opportunities that mHealth may afford for circumventing some of the limitations of current paper-based delivery [26], there is a paucity of evidence demonstrating the comparative benefits of deploying digitized versions of CCM on health service utilization and associated patient costs. To address this evidence gap in a pragmatic cluster-randomized trial, we will evaluate the added value of an electronic CCM App (truncated to SL eCCM App) developed as part of the Supporting Low-cost Interventions For disEase control (Supporting LIFE) program. As well as contributing to the broader mHealth literature, we anticipate that trial findings will provide Malawi’s mHealth Working Group with empirical data, which can be used to inform policy regarding the opportunities to Malawi of introducing such interventions for CCM. Our hypothesis is that adding the SL eCCM App to sick child assessments will increase urgent referral rates and reduce re-consultation and hospitalization rates.

The main objectives of this trial were to determine the:▪ Added value of the SL eCCM App (used with paper-CCM) on referral, re-consultations and hospitalization rates among acutely unwell children aged under 5 years, compared with paper-CCM alone▪ Factors influencing caregivers’ decisions to comply with urgent referral recommendations▪ Direct and indirect costs to caregivers presenting to higher-level facilities and/or re-attending village clinics after the index visit when using paper-CCM and the paper-CCM + SL eCCM App

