### Outcome measures

#### Main outcomes

▪ Urgent referrals to higher-level facilities in the 7 days following the index visit, ascertained from abstraction of patient records 2 weeks after the index visit.*◦ Caregiver-completed referrals in the 7 days following the index visit, determined from abstraction of patient records (i.e., caregivers who were urgently referred and who presented)◦ Caregiver self-referrals to primary or secondary health facilities (i.e., parents/caregivers of children not urgently referred at the index visit, but who presented anyway)
▪ Re-consultations at village clinics due to deterioration of illness, and hospitalizations in the 7 days following the index visit ascertained from abstraction of patient records 2 weeks after the index visit

*Primary outcome measure used to determine the number of participants needed to power the trial.

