#### Statistical/analysis methods

Primary outcome data will be evaluated using pairwise comparisons during the control and intervention periods. Analyses will be conducted at the level of the HSA, taking into consideration the number of index visits that occurred during each period, and will include descriptive statistics relating to each outcome (i.e., referral, re-consultation and hospitalization rates); tests of differences by control/intervention period, and multivariate modeling to allow for adjustment of potential confounding factors within each period. Bivariate descriptive statistics will present proportions for categorical variables or means/standard deviations for continuous and categorical data (respectively), for control/intervention periods. Measures of change will be calculated and two-proportion z-tests or chi-square tests will be used to measure unadjusted differences (depending on test assumptions met). We will conduct multivariate analysis using linear regression to evaluate change in outcomes adjusted for composition of children at each HSA by age, gender, symptoms, location (urban/rural) and proximity to the nearest higher-level health facility. For these models, assumptions will be tested, transformations of variables will be made if needed, and a-priori confounders will be evaluated for inclusion in models. Effect modification will be tested by interactions with age and gender. A secondary analysis will be done at the level of the child adjusting for HSA as a cluster variable. Potential confounders and effect modifiers will also be tested in these models. Data analysis and reporting will be conducted with Consolidated Standards of Reporting Trials (CONSORT) [51].

A cost-consequence analysis will be conducted to report the costs and consequences under the control and intervention. All costs of seeking and receiving care for the control and intervention groups will be calculated separately in a disaggregated way at the household level. Direct costs (e.g., out-of-pocket payments and transportation costs), indirect costs (e.g., costs of parent/caregiver productivity loss) and consequences (e.g., hospitalization days) collected through the PCQ will be compared between parents/caregivers enrolled in the control and intervention phases.

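### The protocol does not settle whether it has one primary outcome or three, and it claims 80% power for three outcomes while giving rates only for urgent referral

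*Protocol article*

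**What the plan says.** Four places in the protocol article bear on this point.

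- **Main outcomes.** Urgent referral, with completed referral and self-referral nested beneath it, is listed beside re-consultation and hospitalization. Only urgent referral carries the asterisk, explained as "Primary outcome measure used to determine the number of participants needed to power the trial".
- **Sample size.** The wording turns plural: "Our sample size estimation is based on change in proportions of the primary outcomes expected pre and post intervention". It continues "Assuming an alpha of 0.05, 97 HSAs would provide 80% power". The effect to which that power applies is given as a "minimum detectable rate of change between 6 and 7% in referral, re-consultation and hospitalizations (one-sided test"). The supporting rates concern one outcome only. The control value is "We assumed a 1% urgent referral rate". The target is drawn from the statement that "an urgent referral rate of 8% has been estimated as a reasonable consensus referral rate at clinics in sub-Saharan Africa".
- **Statistical/analysis methods.** The section opens with the analysis of primary outcome data and, in describing that analysis, lists referral, re-consultation and hospitalization rates together. It gives no order and no significance level.
- **Background.** The hypothesis joins the three: "adding the SL eCCM App to sick child assessments will increase urgent referral rates and reduce re-consultation and hospitalization rates". The Discussion reads the results the same way.

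The section on publication policy says that a full statistical analysis plan would be made public before analysis. It is not shown.

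**The concern.** Which outcome is primary is something this document states, and it states it in two ways. The asterisk points to one outcome; the sizing and analysis sections point to three. The hypothesis adds a third possibility, that all three must move together.

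The choice affects both design claims. A single alpha of 0.05 with 80% power is a complete specification for one deciding test. With three, the error rate or the power changes, depending on how the results are combined. Suppose hospitalization falls while referral is unchanged. Under the asterisk the trial has failed; under an any-one rule it has succeeded; under an all-three rule it has failed for a different reason.

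The power claim also lacks support for two of its three outcomes. No baseline rate is given for re-consultation or hospitalization. For referral the 6 to 7% change is used in percentage points (1% rising to 7–8%). A fall of that many points is impossible for any outcome whose control rate is below 6 to 7%.

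**Working it through.** **Inputs.** From Sample size: alpha 0.05 one-sided, power 80%, 97 HSAs needed and 102 planned, change 6–7 points, each HSA its own control. Normal quantiles: 1.645 for one-sided 0.05, 0.842 for 80% power. The correlation between the three test statistics is not given, so it is varied as an assumption.

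**Step 1: reproduce 97.** Use the paired-proportions (McNemar) approximation, with d the change and ψ the discordant proportion:

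n = [(1.645·√ψ + 0.842·√(ψ − d²)) / d]²

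Assume that all discordance runs one way (ψ = d); the protocol does not state this. At d = 0.0625:

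- √ψ = 0.250 and √(0.0625 − 0.0039) = 0.242
- numerator = 0.411 + 0.204 = 0.615
- n = (0.615 / 0.0625)² = 96.8, so 97

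The same formula gives 101 at d = 6% and 87 at d = 7%. So 97 lies within the stated range, with alpha undivided. Other standard forms do not give it: two independent proportions, one-sided, need 131 (1% v 7%) or 108 (1% v 8%). This step shows only that 97 is consistent with one test at the full 0.05. It does not endorse the sizing method.

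**Step 2: three ways to declare success.**

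(a) *Urgent referral alone decides.* Error 5%, power as claimed, 97 unchanged.

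(b) *Any one of three suffices, each at one-sided 0.05.* If independent, 1 − 0.95³ = 1 − 0.857 = 0.143. For equally correlated normal statistics, P(at least one z > 1.645) is:

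| Correlation | 0 | 0.3 | 0.5 | 0.8 |
|---|---|---|---|---|
| Family-wise error | 0.143 | 0.130 | 0.118 | 0.093 |

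Holding 5% by Bonferroni (0.05/3, quantile 2.128) in the Step 1 formula at d = 0.0625 gives n = 138.6, so 139 HSAs against 102 planned. Power at 97 would be about 64%.

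(c) *All three required, each at one-sided 0.05.* The error is at most 5%. Granting each test 80% power, joint power under independence is 0.8³ = 0.512. With equal correlation:

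| Correlation | 0 | 0.3 | 0.5 | 0.8 |
|---|---|---|---|---|
| Joint power | 0.51 | 0.57 | 0.61 | 0.69 |

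These are favourable values for (c), because nothing in the protocol shows that re-consultation or hospitalization has 80% power.

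**Step 3: compare with the text.** Only (a) keeps both 5% and 80% at 97 HSAs, and it matches the asterisk. It does not match the plural in Sample size or the three-outcome power claim there, nor the three-outcome scope of the analysis section.

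**The case against.** A reader might infer that the trial's false-positive rate simply is two to four times 5%. The documents do not support that. It needs a rule under which any one significant outcome counts as success, and no section states one. The asterisk implies a single test at 5%, and the joined hypothesis suggests an all-three rule with error at most 5%. The top of that range also requires counting completed referral and self-referral, which no section calls primary.

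Two further inferences fail. "Effect modification will be tested by interactions with age and gender" has no significance level and no success claim attached, so it cannot be scored as extra confirmatory tests. Nor can one say that the deciding outcome would be picked once the results were known: the protocol promises a public analysis plan before analysis. An alpha split, a testing order or exploratory labels may properly sit there, and their absence from an article is no fault.

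It is also fair to say that the 0.05 is a sizing input, and that in the analysis section the list of three outcomes is attached directly to the descriptive statistics, with tests of differences named as the next item. Reading it as three primary tests is reasonable but not forced.

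What survives is narrower. The document contradicts itself on the number of primary outcomes, and it asserts power for three on the rates of one. A later analysis plan can choose between these statements but cannot follow both.

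**Conclusion.** The point stands as an inconsistency between Main outcomes, Sample size and Statistical/analysis methods, together with an unsupported power claim for re-consultation and hospitalization. It should be corrected.

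The size is conditional on the success rule: no inflation and no loss if urgent referral alone decides; family-wise error up to 14.3% if any one of three suffices; joint power near 0.61 instead of 0.80 if all three are needed. The figures assume normal test statistics with equal, non-negative correlation. The joint-power figure also assumes 80% power for each test. The reproduction of 97 rests on the added one-way discordance assumption.

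**What to change.** In Main outcomes, Sample size and Statistical/analysis methods, name urgent referral as the single primary outcome that decides the trial at the full alpha, as the asterisk already implies. Call re-consultation and hospitalization secondary. In Sample size, change the plural to the singular and limit the 80% power statement to urgent referral. Any testing order among the secondary outcomes can be left to the analysis plan.

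The cost is wording in three sections, with no new data and 97 HSAs unchanged. The small downside is that a fall in re-consultation or hospitalization alone could no longer be presented as confirmatory. If the authors in fact intend all three to be required, they should say so and restate the power on that basis, with baseline rates for the other two outcomes.

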## Methods/design

### Trial design

This is a pragmatic, stepped-wedge cluster-randomized trial assessing the added value of the SL eCCM App (used with paper-CCM) on referral, re-consultation and hospitalization rates of children aged under 5 years, within 7 days of the index visit. This design was chosen due to insufficient human resources to deliver the intervention to all clusters simultaneously [32] and local advice that withholding the intervention to some clusters may negatively affect participation. We aimed to recruit 102 HSAs and collect data on 8000 children from village clinics across two districts in Northern Malawi between July 2016 and February 2017. HSAs were grouped into six geographic-based clusters. Training workshops were conducted prior to the control (paper-CCM) and intervention (paper-CCM + SL eCCM App) in assigned clusters. Clusters were randomly assigned to the timing of crossover from the control to the intervention [32] for covariate equipoise between phases [33]. A nested qualitative study explored HSA and caregiver perceptions of caregiver adherence to urgent referral recommendations; a cost evaluation investigated the financial and time-related costs to caregivers of seeking subsequent health care for their child after the index visit. Figure 1 shows the trial flow chart; Fig. 2 the trial design (before randomization) and Fig. 3 the Standard Protocol Items: Recommendations for Interventional Trials (SPIRIT) Figure. This protocol adheres to the SPIRIT 2013 Statement for clinical trial protocols (Additional file 1) [34].

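### The stated 80% power and 6–7 point detectable change come from a before-after calculation on 97 HSAs, not from the six-cluster stepped-wedge trial

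*Protocol article*

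**What the plan says.** The Trial design section describes a stepped-wedge cluster-randomised trial with this target: "We aimed to recruit 102 HSAs and collect data on 8000 children from village clinics across two districts". The HSAs are grouped into six geographic clusters. The clusters are what is randomised, to the timing of crossover (Randomization, allocation and blinding). Each phase lasts 2 to 7 weeks (Data collection).

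The Sample size section bases its estimate on a change in proportions from before to after the intervention. At an alpha of 0.05 it concludes: "97 HSAs would provide 80% power for a minimum detectable rate of change between 6 and 7% in referral, re-consultation and hospitalizations (one-sided test". The claim is thus made for all three outcomes. The only control rate is for referral: "We assumed a 1% urgent referral rate". The target comes from a benchmark: "an urgent referral rate of 8% has been estimated as a reasonable consensus referral rate". The assumed 6–7 point change "was, therefore, a conservative estimate of this assumption". The software routine is described as suited to longitudinal studies in which each case is its own control.

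The 8000 children come from an expected recruitment rate of 10 per HSA per week (Recruitment). Within the Sample size section, child numbers appear only in the estimate for the cost questionnaire.

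**The concern.** A detectable change belongs to a design. Here the outcome is a rate among children, the randomised unit is one of six clusters, and treatment is confounded with calendar time unless period is modelled. None of these is an input to the stated calculation.

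Readers will use the printed 6–7 points to interpret the result. If the real detectable change is nearer 2 or 3 points, a true rise from 1% to 3% or 4% would wrongly appear beyond the trial's reach, and a null result could be excused as low power. If correlation within clusters is high and unstable over time, the trial may be less sensitive than stated. The text gives no means of telling which applies.

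Two further statements add to this. The effect size is described as cautious although it nearly equals the benchmark. The same figure is also claimed for two outcomes that have no base rate.

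**Working it through.** **1. Reproducing the stated figure.** Inputs from the Sample size section: one-sided alpha 0.05, power 80%, n = 97, base rate 1%, change d = 6–7 points. For one binary before-after pair per HSA,

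n = [1.645·√pd + 0.842·√(pd − d²)]² / d², with pd = p1(1 − p2) + p2(1 − p1) − 2r·√(p1(1 − p1)p2(1 − p2)).

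The within-pair correlation r is not stated, so it is an assumption here.

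| d | r = 0 | r = 0.2 | r = 0.3 |
|---|---|---|---|
| 6 points | 132.9 | 115.4 | 106.7 |
| 6.5 points | 120.1 | 104.7 | 97.1 |
| 7 points | 109.4 | 95.8 | 89.0 |

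At 1% v 7.5% with r = 0.3, pd = 0.0678 and n = 97.1. Two independent proportions, one-sided, would need 131 (6 points) or 108 (7 points) per group. A one-sample test against 1% would need 40 or 32.

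**2. The equivalent SD.** A paired comparison of means on 97 HSAs gives the same answer if the SD of change is d·√97 / (1.645 + 0.842). That is 0.065 × 9.849 / 2.486 = 0.257, or about 26 points (24 to 28 across d = 6 to 7).

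**3. Comparison with the planned data.** The Sample size section assumes 4000 children per phase; 4000/102 = 39.2 per HSA per phase. The sampling SD of an HSA's change is

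√[(0.01 × 0.99 + 0.075 × 0.925)/39.2] = 0.045, or about 4.5 points.

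True differences between HSAs would add to this. To reach 25.7 points they would have to contribute √(0.257² − 0.045²) = 0.253. For comparison, a rate with mean 7.5% has a maximum SD of √(0.075 × 0.925) = 0.263, reached only if every HSA refers all or none of its children.

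**4. Stepped-wedge recalculation.** From the article: 6 clusters, 102/6 = 17 HSAs each, 8000 children. Inferred from the 2-to-7-week phases, because the design figure is not shown: 9 weeks, with one cluster crossing after each of weeks 2 to 7. This gives 8000/54 = 148 children per cluster-week.

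Assumed: HSA ICC 0.02; cluster ICC ρ and cluster autocorrelation (CAC) as tabulated; variance at the mid-rate of 1% and 7%, σ² = 0.04 × 0.96 = 0.0384.

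The covariance of one cluster's nine weekly means is

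V = σ²{ρ[CAC·J + (1 − CAC)·I] + (0.02/17)·J + [(1 − ρ − 0.02)/148]·I},

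where J is the all-ones matrix and I the identity. The SE is the square root of the treatment element of (Σ X′V⁻¹X)⁻¹, where X holds nine week effects and treatment. Detectable change = SE × multiplier: 2.486 (one-sided, normal), 3.073 (one-sided, t on 4 df) or 3.717 (two-sided, t on 4 df). The 4 df is an assumed small-sample correction for six clusters.

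| ρ, CAC | SE (points) | One-sided, normal | One-sided, t | Two-sided, t |
|---|---|---|---|---|
| 0 | 0.74 | 1.8 | 2.3 | 2.8 |
| 0.02, 1 | 0.79 | 2.0 | 2.4 | 2.9 |
| 0.02, 0.8 | 1.00 | 2.5 | 3.1 | 3.7 |
| 0.05, 0.5 | 1.71 | 4.2 | 5.2 | 6.3 |
| 0.10, 0.5 | 2.29 | 5.7 | 7.0 | 8.5 |

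Power for a 6-point change in the last row, with t on 4 df, is 68% one-sided and 44% two-sided. For ρ up to 0.02 with CAC of at least 0.8 it exceeds 98% either way. The blocked-out workshop periods, when no child could be enrolled, are not modelled and would change these figures somewhat.

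**5. The effect size.** The gap from 1% to 8% is 7 points. The assumed change is 6/7 = 86% to 7/7 = 100% of it.

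**The case against.** The article says openly that the calculation is before-after with each case as its own control. It never claims an adjustment for clustering, so a reader who infers that clustering and time were allowed for is not relying on anything in the text. One value per HSA per phase also fits the planned primary analysis, which compares periods at HSA level. Both points stand, so the mismatch is with the randomised design. The fit with the analysis is only partial, however: that analysis would use HSA rates built on dozens of children, whose sampling error is far below the SD the calculation implies.

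The derivation cannot be identified with certainty. No correlation, discordance or SD is stated, and the match at 97 needs a chosen correlation. A continuous HSA-level calculation with an assumed SD near 26 points would do equally well. That also stands, but on either route the number of children, the clusters and time do not enter.

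Two stronger readings are tempting. One is that 6–7 points is too large by some fixed multiple. The article gives no ICC or autocorrelation, and the plausible range runs from well below 6 points to above 7, so no multiple can be supported. The other is that the trial is underpowered, or conversely that its size is shown to be ample. Most scenarios give high power for a rise from 1% to 7%, but the adverse one does not, so neither is established.

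On the effect size, 6 points does stop short of the 8% benchmark; only the 7-point end reaches it.

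**Conclusion.** The concern holds as a mismatch between calculation and design. The arithmetic can be reproduced, but what it reproduces is a paired before-after comparison on 97 HSAs. The 80% power and the 6–7 points therefore do not describe this six-cluster stepped-wedge trial. This is not detail left to a fuller document: the article states both the method and the resulting figure.

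Under low correlation (cluster ICC 0–0.02, autocorrelation 0.8–1) the stated figure is probably too large. At ICC 0.10 and autocorrelation 0.5 it is about right or somewhat too small. These ranges rest on assumed correlations, an inferred 9-week layout, variance at a 4% rate and, where t is used, 4 degrees of freedom.

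Two smaller points stand with it. A change covering 86–100% of the gap to the benchmark is close to the best case and is not a cautious assumption. The claim for re-consultation and hospitalisation has no base rate behind it.

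**What to change.** Replace the power statement with a stepped-wedge calculation for urgent referral. Use 8000 children, six clusters of about 17 HSAs, the actual step layout including the blocked-out workshop periods, period effects, a stated range of cluster ICC and autocorrelation, a small-sample correction for six clusters, and a stated sidedness. Report the detectable change as a range over those inputs.

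Delete the description of the assumed change as conservative. Limit the claim to urgent referral unless base rates for the other two outcomes are supplied.

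Follow-up was complete by 3 February 2017, so the natural places are the statistical analysis plan, which the article promises to publish before analysis, and the results paper. The cost is a short calculation, some rewording and a less definite figure. Enrolment and data collection do not change.
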